## FOLLOW-UP VISITS

During the following visits (V2, V3 and V4), scheduled at 3-week intervals +/- 3 days. Each patient will benefit from an evaluation:

- **the intensity of the pain thanks to the VAS before each FR vs SM session over the last 7 days,**
- **a compendium of adverse events (AEs).**

**Then the patient will benefit from a FR vs SM session performed by the reflexologist.**

At visit 4, the patient will benefit from his last session of FR vs SM, the subjective nociceptive threshold and heat tolerance will be assessed before and after the session.

## END-OF-RESEARCH VISIT

The last study visit (V5) scheduled 3weeks +/- 3 days after V4 will assess all outcomes assessed in V1.

The purpose of this study is to evaluate chronic pain and not acute pain in Parkinson's patients. We will compare pain over the last 7 days of each visit throughout the study and more specifically before and after overall management with RP versus MS. The pain assessment will be carried out blinded by a clinical research associate who works in [name] department and who regularly treats Parkinson's patients.

The patient will therefore not benefit from a FR vs SM session at this visit.

He will also have an evaluation of the subjective nociceptive threshold and the tolerance to heat to observe a possible residual effect of the management by foot reflexology.

At the end of this visit, the patient will have completed his participation in the study.

Patients randomized to the MS group will be able to benefit from a PR session following their participation.

The care of patients will be continued as part of the routine care for their Parkinson's disease, at the end of this visit.

There is no deferral period for this study.

## RULES FOR STOPPING A PERSON'S PARTICIPATION IN RESEARCH

The rules for stopping participation in research will be as follows

- Withdrawal of consent (voluntary decision of the participant)
- Adverse event not allowing the patient to continue
- Modification of the anti-parkinsonian treatment during the study
- Major deviation from the protocol.

In the event of termination of participation in the study, patients will continue their usual medical follow-up, without any modification. An end-of-study sheet will be completed.

There are no plans to replace patients who leave the study prematurely.

## CONSTRAINTS RELATED TO THE SEARCH AND POSSIBLE COMPENSATION OF PARTICIPANTS

The patient will be required to attend all 5 visits to benefit from the FR vs SM sessions and research-related assessments. He or she will also have to perform 2 fMRI examinations and agree to be informed if an abnormality is detected during the examination.

The patient will have an assessment of pain tolerance. This evaluation may be unpleasant but only lasts a few seconds for the patient.

Transport will be reimbursed in actual costs.

There is no provision for compensation for participants in this research.

Patients will not be registered in the national file of people who are suitable for research.

There will be no deferral period for another research at the end of this research. Patients should not participate in a clinical trial at the same time.

## 10. MANAGEMENT OF ADVERSE EVENTS / ADVERSE REACTIONS / INCIDENTS

Adverse events / adverse effects / incidents must be reported to the various health vigilance circuits applicable to each product or practice concerned (vigilance of care, pharmacovigilance, materiovigilance, haemovigilance, cosmetovigilance, etc.) in accordance with the regulations in force.

Registrants must specify that the patient is included in a clinical trial and accurately identify the clinical trial concerned.

If the investigator becomes aware of a patient safety breach in the course of the research, the investigator must promptly inform the sponsor.

**11. STATISTICAL ASPECTS**

### CALCULATION OF THE STUDY SIZE

We will include 30 patients in this study divided into 2 groups of 15 patients. The calculation is based **on the expertise of Centre Expert Parkinson** in Parkinson's disease and more particularly in the associated pain and **on data from the literature**. In assessing pain in

Parkinson's disease by means of VAS, an average reduction of 20 mm on EVA is considered to be

clinically significant (bilateral test), with an alpha risk = 0.05 and a beta risk = 0.20. The standard deviation is 1.5 on an AVE in Parkinson's patients.

With these data and by calculating the number of subjects, 12 patients per group appear to be necessary. With an estimated risk of patients leaving the study at 25%, it is therefore necessary to recruit 15 patients per group.

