**4. JUDGING CRITERIA**

### 4. PRIMARY OUTCOME

The primary outcome of this study is the variation in mean pain intensity during the previous week, rated on an VAS (from 0 = no pain to 10 = maximum imaginable pain), before and after management between the 2 groups of patients (FR vs SM). Pain intensity on VAS is a validated clinical criterion for the global assessment of the discriminative and emotional aspects of pain *[Price 1994].*

We chose to assess the intensity of the overall pain and not the intensity of the different types of pain. Indeed, we believe that this type of intervention can have a non-specific effect on pain and therefore reduce the perception of pain in general and thus improve the daily life of patients. The variation corresponds to the raw delta between the VAS score at baseline (V1) and that after the 4 sessions of FR vs SM at the last visit (V5).

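### The step from 12 to 15 per group does not cover the stated 25% loss (about 11 remain), and the 20 mm and the SD of 1.5 are not tied to the change being compared

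*Protocol*

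**What the plan says.** Protocol section 11, Calculation of the study size, gives these elements:

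- Effect: "an average reduction of 20 mm on EVA is considered to be" clinically significant, with a two-sided test.
- Error rates: "with an alpha risk = 0.05 and a beta risk = 0.20".
- Spread: "The standard deviation is 1.5 on an AVE in Parkinson's patients". No unit is attached, and the text does not say whether this describes a single score or a change.
- Result: "12 patients per group appear to be necessary".
- Allowance for loss: "With an estimated risk of patients leaving the study at 25%, it is therefore necessary to recruit 15 patients per group". The total is 30.

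Three other places bear on this. Section 4, Primary outcome, defines the endpoint as the raw difference in VAS between V1 and V5, on a scale from 0 to 10. Section 11, Statistical methods used, compares those differences between FR and SM with a Wilcoxon-Mann-Whitney test. Section 9, on stopping a person's participation, says that patients who leave early are not replaced. The VAS form in the annex records the score in mm out of 100.

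**The concern.** Two things in the paragraph do not fit.

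First, the recruitment figure is presented as following from 12 evaluable patients and 25% loss, but 15 per group less a quarter is fewer than 12. Nothing later makes up the gap, because leavers are not replaced.

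Second, the primary test compares two groups on a change score. The inputs that such a test needs are the expected FR-SM difference in change and the SD of that change. The paragraph offers a clinically relevant reduction and an SD on the VAS, without saying that they are these two quantities, and in what appear to be different units.

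At stake is how the result can be read. The trial is exploratory, but it states a formal alpha, beta and N, and section 2 presents the data as the basis for a larger study. A reader should be able to see which difference the trial could detect and under what assumption about spread. The designers of the next trial should not inherit inputs whose meaning is unclear.

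**Working it through.** **Inputs (Protocol section 11).** Difference 20 mm = 2.0 points on 0-10; SD 1.5; two-sided alpha 0.05 (z = 1.960); beta 0.20 (z = 0.842); 12 evaluable per group; 25% loss; 15 recruited per group.

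**Unit of the SD.** If 1.5 were in mm, n = 2 x (1.960 + 0.842)² x (1.5/20)² = 0.09, i.e. 1 per group. The stated 12 makes sense only if 1.5 is on the 0-10 scale, i.e. 15 mm.

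**Reproducing the 12.** Take 2.0 as the between-group difference and 1.5 as the SD of what is compared.

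- Normal formula: 2 x 7.849 x (1.5/2)² = 8.8, so 9.
- t-test: 9.9, so 10.
- Wilcoxon-Mann-Whitney from the t-test figure with relative efficiency 0.955: 9.9/0.955 = 10.4, so 11. With the conservative 0.864: 9.9/0.864 = 11.4, so 12.
- Noether's formula: P(X<Y) = Φ(2/(1.5√2)) = Φ(0.943) = 0.827. Total N = 7.849/(12 x 0.25 x 0.327²) = 24.5, i.e. 12.2 per group.

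So 12 is consistent with the stated inputs for the planned rank test.

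**The allowance for loss.**

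- As done: 12 x 1.25 = 15.
- Correct: 12/(1 - 0.25) = 16 per group, 32 in total.
- Left from 15 at 25% loss: 15 x 0.75 = 11.25, so about 11.
- Loss that 15 does cover: 1 - 12/15 = 20%.

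**Power on the same inputs (difference 2.0, SD 1.5).** The Mann-Whitney figures are simulated with normal data.

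| n per group | t-test | Mann-Whitney |
|---|---|---|
| 10 | 80% | 76% |
| 11 | 84% | 82% |
| 12 | 88% | 85% |

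The slip costs about 3 percentage points and leaves power just above 80%.

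**Sensitivity to what the two inputs mean.** The values below are assumptions; the Protocol gives neither a V1-V5 correlation nor an expected sham response. If 1.5 is the SD of a single score, the SD of the change is 1.5 x √(2(1 - ρ)): 1.90 at ρ = 0.2, 1.77 at 0.3, 1.50 at 0.5 and 1.16 at 0.7. Mann-Whitney power with 11 per group:

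| Between-group difference | SD of change | Power |
|---|---|---|
| 20 mm | about 12 mm | about 96% |
| 20 mm | 15 mm | about 82% |
| 20 mm | about 18-19 mm | about 62-68% |
| 15 mm | 15 mm | about 58% |
| 10 mm | 15 mm | about 30% |

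**The case against.** The strongest reply is that the confirmed error has almost no consequence. It amounts to one patient per group, power stays above 80% on the Protocol's own inputs, and the trial is labelled exploratory and a pilot. The analysis is by intention to treat, so leavers are not automatically dropped, and the handling of missing values may be set out elsewhere. It is also common to use a clinically relevant threshold as the target difference between groups. The two-sided test and the figure per group fit that reading.

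Most of this stands, and it sets the size of the point. It does not repair the paragraph: the paragraph itself treats leavers as lost when it inflates the number, and its recruitment figure does not yield the number that it says is needed. The between-group reading is plausible, but the reader has to supply it.

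Two stronger readings are tempting and should not be made. A reader might infer that 12 does not follow from the inputs, because the usual normal and t-test formulas give 9 or 10. The planned test is Wilcoxon-Mann-Whitney, for which about 11 to 12 is right. A reader might also infer that the Protocol expects pain relief under sham, so that 20 mm cannot be the between-group difference. The benefit/risk section says that control patients will benefit from care, follow-up and massage, but elsewhere the Protocol uses the same verb for simply receiving an fMRI or an evaluation. The justification of methods only reports the critics' placebo argument. Neither passage states an expected sham improvement.

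**Conclusion.** The allowance for loss is wrong as written: 25% loss from 15 per group leaves about 11, not 12, and 16 would be needed to keep 12. This is certain from the Protocol's own figures and small in effect, at one patient per group and about 82% instead of 85% Mann-Whitney power. Those power figures assume normal data, a 20 mm FR-SM difference in V1-V5 change and a 15 mm SD of that change.

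The second part is an omission of meaning, not a proven wrong value. Section 11 does not state that its 20 mm and 1.5 are the difference and SD of the endpoint tested, and it mixes units. A reader might go further and conclude that the trial is underpowered. The documents do not support that: the lower powers in the sensitivity table depend on a correlation or a smaller difference that no section gives, and a correlation of 0.5 leaves the SD of the change at exactly 15 mm.

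**What to change.** Rewrite the paragraph in section 11 and keep 30 patients:

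- State that 15 per group leave about 11 evaluable at 25% loss, and 12 only if loss is 20%.
- State that 11 per group give about 80% power with the Mann-Whitney test, two-sided 0.05, for a between-group difference of 20 mm in V1-V5 change, assuming an SD of that change of 15 mm.
- Use mm throughout, and give the source of the SD. If the source reports the SD of a single score, say so and state the correlation assumed.
- Name the method behind the 12, since the usual t-test formula gives a different number.
- Add the sensitivity table above, labelled as assumptions.

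The cost is one paragraph and a five-line table. The stated power becomes slightly less favourable, and no patient, visit or analysis is added. If the sponsor prefers to keep 12 evaluable at 25% loss, the alternative is 16 per group, 32 in total.

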**THIS CALCULATION WAS CARRIED OUT BY THE RESEARCH METHODOLOGICAL SUPPORT UNIT.**

### STATISTICAL METHODS USED

Data analysis:

The data processing that will be carried out will be in accordance with the MR-001 reference methodology and therefore meets the CNIL and GDPR expectations, the data in this study will be pseudonymized and protected. A randomization list will be created to randomly determine patient groups.

A detailed flow-chart will describe the flow of subjects in the study. In particular, the number of subjects screened for eligibility, the number of eligible subjects, the number of subjects included and followed up at each visit will be mentioned. The reasons for refusal to participate and to leave the study will be described at each stage.

A descriptive analysis of the entire recruited population will be carried out to verify if there are any deviations from the protocol at the time of inclusion. Quantitative variables will be expressed as ± average standard deviation, range, medians and interquartile ranges, and qualitative variables will be expressed as numbers and percentages.

The analysis is conducted on the intention-to-treat population.

To meet the main objective, we will first describe the VAS score at Baseline (V1) and after all PR sessions (V5) by means of a "box plot" graph. This is in order to better understand the distribution of scores in the 2-stroke and in the 2 groups (as well as 4 box plots). Then we will calculate and describe the variations between V5 and V1. The variation between V1 and V5 is defined by the crude delta between these 2 visits. Finally, we will perform a non-parametric Wilcoxon Mann Whitney test to compare the distribution of variations between the 2 groups of patients.

To meet the secondary outcomes:

1. We will calculate the number of patients with a minimum of 30% improvement on the VAS score between V1 and V5. Thus, if (V5-V1)/V1 is greater than or equal to 30%, the patient is considered to be a responder. We will compare these responder rates between the 2 groups of patients using a Chi2 test.
2. We will perform a non-parametric Wilcoxon Mann Whitney test to compare the distribution of variations at each visit (delta with baseline) between the 2 groups of patients: i.e. 4 tests.
3. For the KPPS and BPI scores and the 3PDQ, we will perform the same analyses as the primary outcome because they are quantitative scores.
4. For the subjective pain perception threshold to heat and heat tolerance. We will perform the same analyses as the primary outcome as these are quantitative scores. 5. For the consumption of analgesics, which will be considered as several qualitative variables (e.g. taking paracetamol yes/no, aspirin taking yes/no), we will compare the proportion of patients taking each analgesic between the 2 groups by means of Chi2 tests.
5. The analyses regarding the CPAQ-8 score will be the same as those for the primary objective as it is a quantitative score. As the anxiety and depression scores of the HAD scale are quantitative variables, they will be analysed in the same way as the primary outcome.
6. As imaging results are quantitative variables, we will analyze them in the same way as for the primary purpose.
7. Personality profile results will be analyzed using a nonparametric Wilcoxon Mann Whitney test

For the study as a whole, the significance threshold is set at 0.05 (bilateral).

The statistical analysis will be conducted by [name] from the MeDatAS – CIC – CHU Toulouse team. Analyses will be conducted using SAS analysis software version 9.4 or later.

All analyses of neuroimaging data will be carried out within the ToNIC unit (Inserm/UPS UMR1214):

- the structural and activation images obtained in MRI for each subject will be normalized and smoothed using the Statistical Parametric Mapping ((SPM) software Wellcome Department of Cognitive Neurology, University College, London, UK).
- The resting state images fMRI will be analyzed using a model-dependent method called "seed-tovoxels" using the Conn software version 18b (https://www.nitrc.org/projects/conn). The seeds will be determined according to anatomical atlases to identify the brain areas of interest (default mode network, sensorimotor network). The connectivity between these seeds and the rest of the brain voxels will be explored.

These images will then be used to perform a t-corrected test for multiple comparisons to compare the cards [after – before] support. Thus, the intensity and size of the synchronous activity of brain areas functionally connected to the areas of interest of the reflex zones stimulated on the foot can be determined. Areas of interest are defined anatomical areas in known and classic stereotactic spaces in neuroimaging.

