**6. ELIGIBILITY CRITERIA**

## INCLUSION CRITERIA

- Men and women ≥ 18 years old.
- Patients with no disabling dyskinesias judged by the investigator.
- Patients with chronic pain of any origin, regardless of the pathophysiological mechanism, for at least 3 months with VAS ≥ 4.
- Patients whose anti-Parkinson's treatment has been stable throughout the duration of the study and at least for 4 weeks.
- Person affiliated to or beneficiary of a social security scheme.
- Free, informed, written, and signed consent by the participant and the investigator (no later than the day of

, inclusion and prior to any review required by the research).

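### The analysis is called intention-to-treat, but the stopping rules end follow-up of randomised patients, so no V5 pain rating is planned for them

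*Protocol*

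**What the plan says.** Protocol section 11, Statistical methods used, sets the population and the primary analysis:

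- Population: "The analysis is conducted on the intention-to-treat population".
- Primary variable: "The variation between V1 and V5 is defined by the crude delta between these 2 visits".
- Primary test: "we will perform a non-parametric Wilcoxon Mann Whitney test to compare the distribution of variations between the 2 groups of patients".

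Protocol section 9, Rules for stopping a person's participation in research, lists four reasons for ending participation. Two are withdrawal of consent and an adverse event that prevents continuation. The other two are "Modification of the anti-parkinsonian treatment during the study" and "Major deviation from the protocol". On what follows it says: "In the event of termination of participation in the study, patients will continue their usual medical follow-up, without any modification". An end-of-study sheet is filled in, and leavers are not replaced.

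Protocol section 6, Inclusion criteria, also admits "Patients whose anti-Parkinson's treatment has been stable throughout the duration of the study and at least for 4 weeks". Randomisation takes place at the inclusion visit, once eligibility has been checked (section 5, Methods for randomization).

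**The concern.** An intention-to-treat comparison needs the outcome of every randomised patient, or at least an attempt to collect it. Here two of the four stopping reasons are events that normally define a per-protocol exclusion. The rule applies them by ending data collection, not only the sessions. The primary variable is a difference that needs an observed V5 rating, so a patient stopped at V3 has no primary outcome even if willing to give one.

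This matters if leaving is related to pain. The protocol's own instruments suggest that it could be. The 3PDQ asks whether the pain improves with antiparkinsonian drugs, and the KPPS scores pain in off periods, so a treatment change may follow from the symptom being measured. The term major deviation is not defined in the stopping rules. Section 9 has the randomisation site report the allocated group to the investigator, whereas section 5 says that only the practitioner is told. A decision to remove a patient might therefore be made with knowledge of the arm.

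The inclusion wording adds a second route. Stability throughout the study cannot be known at randomisation. Read literally, it would let a randomised patient be declared ineligible afterwards.

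**Working it through.** **1. Is V5 lost when participation ends?** No sentence says that V5 is omitted, so this is a reading of several sections together.

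- Research timeline: participation lasts 12 weeks.
- Summary table of participant monitoring: V5 is at week 12.
- End-of-research visit: participation is complete at the end of V5.
- Stopping rules: after stopping, only usual medical follow-up and an end-of-study sheet are described.
- Calculation of the study size: extra patients are recruited for those who leave, so leavers are counted there as lost to the analysis.

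V5 lies inside participation. Ending participation earlier ends the VAS schedule.

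**2. The plan's own figures.** Inputs from Calculation of the study size: difference 20 mm, that is 2 points on the 0-10 scale; SD 1.5, read as points; two-sided alpha 0.05; power 80%; leaving 25%.

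- Two-sample t-test: 9.89, so 10 per group.
- Adjusted for the Mann-Whitney test with efficiency 0.864: 9.89 / 0.864 = 11.4, so 12 per group. The stated 12 is reproduced.
- Inflation: 12 x 1.25 = 15, the stated figure. (Dividing, 12 / 0.75 = 16. This is a side point.)

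**3. How many have no primary outcome?**

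- 30 x 0.25 = 7.5, so 7 to 8 patients, for all four stopping reasons together. The protocol gives no split by reason.
- Left for the V5 comparison: 30 x 0.75 = 22.5, or 15 x 0.75 = 11.25 per group.
- Simulated Mann-Whitney power for 2 points, SD 1.5 (20,000 runs): about 82% with 11 per group, 85% with 12 and 92% with 15. Power among those left is not the main problem.

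**4. Possible bias.** Assumptions not in the protocol: 25% leave in each arm, completers differ by 2.0 points, and leavers would have differed by d.

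All-randomised difference = 0.75 x 2.0 + 0.25 x d

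| d | All-randomised difference | Completers' result relative to it |
| --- | --- | --- |
| 0 | 1.50 | 2.0 / 1.50 = 1.33 (33% too high) |
| 1.0 | 1.75 | 2.0 / 1.75 = 1.14 (14% too high) |
| 2.0 | 2.00 | 1.00 (no overstatement) |

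**5. Effect on the test when there is no true difference.** Simulation with 4 of 15 leaving each group, SD 1.5:

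- Leaving at random in both groups: type I error about 4.5%.
- In one group, the four most extreme values in one direction leave: spurious difference about 0.63 points, type I error about 19%.

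The second case is deliberately extreme. It marks an outer bound and is not a forecast.

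**The case against.** The strongest reply is that the protocol nowhere excludes patients without V5. A reader might infer that it specifies a completers analysis and drops leavers unremarked. The documents do not support that. A rule for missing values may stand in a statistical analysis plan that is not shown, and its absence from the protocol is no fault. The protocol also promises a flow chart with reasons for leaving and an explanation for each missing datum. What remains is narrower: an analysis plan can impute a V5 value, but it cannot recover a rating that the stopping rules do not have collected.

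Other limits stand:

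- It would be wrong to say that the V2 to V4 ratings of leavers are unused. The second secondary analysis tests the change from baseline at each visit, so they can contribute there. They are absent only from the primary test.
- The 25% covers withdrawal of consent and adverse events too. It cannot all be charged to treatment changes and deviations.
- Analgesics of any class are allowed (section 8), and changing them is not a stopping reason. The most direct response to uncontrolled pain therefore keeps the patient in the study. A link between leaving and outcome is plausible but not shown.
- Replacing the Mann-Whitney test with a mixed model in a 30-patient pilot would be a matter of preference. It is not needed to remove the contradiction.
- Section 8, Associated treatments/procedures allowed, states in-study stability as a condition of conduct. The inclusion wording may therefore be only awkward. It calls for reconciliation, not for choosing a different treatment rule.

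**Conclusion.** The point holds. Followed as written, the stopping rules leave randomised patients without the V5 rating that the primary variable requires, and this conflicts with the stated intention-to-treat analysis. About 7 to 8 of 30 patients could be affected at the protocol's own leaving rate, counting all reasons.

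The size of any bias is not known. Under the assumptions shown, the completers' result is too high by 0 to 33%; the upper end requires that leavers have no treatment difference at all. If leaving is unrelated to outcome, there is no material bias. A reader might take the overstatement of one third as the expected result, but the documents give no basis for placing the truth at that end of the range.

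The conclusion rests on reading the end of participation as the end of the VAS schedule. The protocol does not say this in words, but its timeline, visit table and final-visit section all point that way. The issue should be put right because the protocol intends these results as preliminary data for a larger study.

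**What to change.** Reconcile the stopping rules in section 9 with the population statement in section 11:

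- Distinguish the end of sessions from the end of data collection.
- Seek the scheduled VAS ratings through V5 from every randomised patient who has not withdrawn consent to them, whatever the reason sessions stopped.
- Include these ratings in the primary Mann-Whitney comparison. If this is not done, do not call the analysis intention-to-treat.
- Reconcile the stability wording in section 6 with Methods for randomization (section 5), the allowed-treatments text (section 8) and the stopping rules (section 9), so that it is not used to exclude a patient after randomisation.

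No change to the clinical reasons for stopping is proposed. The cost is amendment wording and a few V5 visits that are already in the schedule. One consequence should be foreseen: if 4 of 15 reflexology patients gained nothing, the all-randomised difference would be 2 x (1 - 4/15) = 1.47 points, and simulated power with 15 per group about 64%.

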## EXPECTED BENEFITS

This study proposes an **innovative approach** to the management of chronic pain for Parkinson's patients in this study by RP.

▪ **Expected outcomes directly for patients in the study**

Through this project, we propose a FR protocol whose content has been standardized, exploring the effectiveness of this management through different markers and scales, compared to an SM. This study will thus make it possible to better specify the uses and represents an essential step in validating the impact of FR on patients' chronic pain in a comparative approach. Based on experience and observation, we postulate that this management (of 4 FR sessions) should lead to clinically relevant improvement in chronic pain.

- **Preliminary data: solid basis for a larger study**

All the elements collected will constitute preliminary data that will allow us to subsequently design a larger research project. These data will make it possible to validate their effectiveness in terms of benefits for patients (reduction of chronic pain, quality of life, stress management), as well as to propose brain imaging biomarkers of potential brain changes that occur during pain reduction in PD patients.

- **Expected long-term impact on the Parkinson's patient population** In the population of Parkinson's patients with chronic pain, the use of FR could be beneficial in terms of:
- **by improving the perception of pain and therefore the daily life of patients,**
- **by avoiding the use of pharmacological analgesics and their possible side effects.**

In the long term, the challenge is to provide new tools in the management of chronic pain, to have reliable information to better inform patients and to enable health professionals to recommend RP as a complementary therapeutic method in an informed manner.

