## INCLUSION VISIT / RANDOMIZATION PROCESS

### Collection of consent

Prior to any research-related review, the investigator obtains the free, informed, and written consent of the participant (or his/her legal representative if applicable).

If the participant gives his or her consent to participate, the participant and the investigator write their first and last names in plain text, date and sign the consent form. This must be signed BEFORE CARRYING OUT ANY CLINICAL OR PARACLINICAL EXAMINATION REQUIRED BY THE

RESEARCH. The consent is signed in 2 copies, one of which is delivered to him in person.

Once eligibility has been verified and consent has been signed, randomization can take place. When an investigator wishes to perform randomization after verifying the participant's eligibility, they log on to the website: http:// XX . The investigator completes the "randomization" web page after having previously confirmed all the patient's eligibility criteria on the site. After validation of the content, randomization is performed and the site immediately communicates to the investigator the unique number of the participant in the research, the result of the randomization, in particular the procedure group allocated to the patient.

Following randomization, each participant will benefit from an evaluation at inclusion:

- **Socio-demographic data (age, sex).**
- **PD treatments, analgesic treatments and concomitant treatments in progress.**
- **Pain that includes:**
  - The maximum and average VAS over the previous week *[Price 1994]*
  - The KPPS: a scale that assesses the intensity of pain in PD *[Chaudhuri 2015]*
  - The BPI *[Brasseur 1997]* - The Mac Gill *[Turk 1985]*
  - CPAQ-8: a questionnaire that assesses the extent to which the person "accepts" the presence of pain *[McCracken 2004]*
  - 3 PDQ (Parkinson's Primary Pain Questionnaire)
- **Motor state, anxiety and depression which include:** - The MDS UPRDS III scale *[Defebvre 2018]*

- HAD (Hospital Anxiety and Depression) scale *[Lépine 1985]*

- **the intensity of the pain thanks to the VAS before each FR vs SM session (from V1 to V4) over the last 7 days,**
- **an assessment of the subjective pain perception threshold and heat tolerance via the thermotest before and after the FR vs SM session**
- **An assessment of the personality profile using the TCI personality questionnaire.**

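### The primary Mann-Whitney test on the raw V1-V5 VAS change is valid, but adjusting for the V1 VAS already collected would usually give more power at no extra cost to patients

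*Protocol*

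**What the plan says.** In the Protocol, section 11, Statistical methods used, the primary variable is unadjusted: "The variation between V1 and V5 is defined by the crude delta between these 2 visits". V1 and V5 scores are shown as box plots, the changes are described, and then: "Finally, we will perform a non-parametric Wilcoxon Mann Whitney test to compare the distribution of variations between the 2 groups of patients". The research summary and the abstract name the same test. The significance level is two-sided 0.05.

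The V1 score is available for everyone. The inclusion evaluation lists "The maximum and average VAS over the previous week", and the monitoring table has VAS at every visit from V1 to V5. Patients enter with chronic pain "for at least 3 months with VAS ≥ 4". The randomisation section describes 1:1 allocation and names no stratification factor.

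For the pain kinetics the same test is repeated by visit, to "compare the distribution of variations at each visit (delta with baseline) between the 2 groups of patients: i.e. 4 tests". On the purpose of the data, the Expected benefits section says: "All the elements collected will constitute preliminary data that will allow us to subsequently design a larger research project".

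**The concern.** A raw change score gives the baseline a fixed weight of one. Unless V1 and V5 are almost perfectly correlated, that weight is too large, and the noise of the V1 measurement enters the comparison. ANCOVA estimates the weight from the data and so usually has a smaller error variance. With 15 recruited per arm and losses expected, power and interval width are worth protecting.

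A chance difference in V1 pain between two small arms also carries over into the contrast of raw changes in the one trial that is run; adjustment removes it. Finally, an adjusted difference in VAS points, its interval and a residual SD are what the sizing of a larger trial would use.

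The protocol itself fixes the primary test, so the choice of method is not a detail left to an analysis plan that is not at hand.

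**Working it through.** **Inputs from Calculation of the study size.** Difference 20 mm, that is 2 points on the 0-10 scale; SD 1.5, read as points, without saying whether it is the SD of the score or of the change; two-sided test "with an alpha risk = 0.05 and a beta risk = 0.20"; 12 evaluable per group; 25% loss; 15 recruited per group.

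**Assumed.** The V1-V5 correlation ρ, which the documents do not give; equal SDs at V1 and V5; normal errors unless stated.

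**The protocol's own figure.** n per group = 2 × 1.5² × (1.960 + 0.842)² / 2² = 8.83. The two-sample t-test needs 9.89, so 10. Dividing 9.89 by the lower bound of the Mann-Whitney efficiency, 0.864, gives 11.45, so 12. The stated 12 is reproduced. With 25% loss, 15 × 0.75 = 11.25 remain, so both 11 and 12 per arm are used below.

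**Variance.** With score SD σ, the raw change has variance 2σ²(1 − ρ). After adjustment the residual variance is σ²(1 − ρ²). The ratio is (1 + ρ)/2: 0.65, 0.75, 0.85 and 0.90 for ρ = 0.3, 0.5, 0.7 and 0.8.

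**Simulated power, difference 2 points, two-sided 5%** (good to about one percentage point):

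| 1.5 read as | n per arm | ρ | Mann-Whitney on change | ANCOVA |
|---|---|---|---|---|
| SD of score | 11 | 0.3 | 69% | 87% |
| SD of score | 11 | 0.5 | 81% | 92% |
| SD of score | 11 | 0.7 | 96% | 98% |
| SD of change | 12 | 0.3 | 85% | 97% |
| SD of change | 12 | 0.5 | 85% | 94% |
| SD of change | 12 | 0.7 | 85% | 91% |
| SD of change | 12 | 0.8 | 85% | 89% |

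The type I error of ANCOVA was about 5%. For a difference of 1.5 points, 12 per arm and ρ = 0.5, power goes from 61% to about 75%. The mean half-width of the 95% CI (12 per arm, ρ = 0.5) falls from 1.25 to 1.12 points, where 1.25 belongs to the mean difference in raw change.

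**Effect of the entry threshold.** Truncating V1 at 4 (assumed mean 6, SD 1.5 as score SD, 12 per arm, ρ = 0.5) leaves a gain from 87% to 94%.

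**How much is adjustment and how much is the change of test.** With 1.5 as the change SD, 11 per arm and ρ = 0.7, power is 82% for Mann-Whitney, 85% for an unadjusted t-test and 89% for ANCOVA. About 3 of the 7 points come from leaving the rank test.

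**Non-normal residuals** (12 per arm, change SD 1.5, ρ = 0.7). With t residuals on 3 df, ANCOVA has 92% and Mann-Whitney 94%. With exponential residuals, 89% and 92%. At ρ = 0.3 ANCOVA stays ahead in both shapes (95% against 91%, and 94% against 90%).

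**Chance imbalance.** With 15 per arm and an assumed V1 SD of 1.5, the SD of the baseline difference between arms is 1.5 × √(2/15) = 0.55 points. An imbalance of that size shifts the raw-change contrast by (1 − ρ) × 0.55 = 0.27 points at ρ = 0.5, or 14% of the 2-point target.

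**The case against.** The strongest defence is that nothing here is wrong. A Mann-Whitney test on change in a randomised 1:1 comparison controls its error rate, matches the declared outcome and is a reasonable choice for about a dozen patients per arm on a bounded scale. If 1.5 is the SD of the change, it already has about 85% power at 12 per group, above the 80% target. That stands, and so the point is one of efficiency. It also stands that ρ is unknown, that the gain is small at 0.8 and above, that part of it is not baseline adjustment, and that with clearly non-normal residuals and high correlation plain ANCOVA can lose slightly. Keeping a rank test as sensitivity analysis does not recover power lost in the primary analysis.

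A confidence interval could accompany the planned test (a Hodges-Lehmann shift) and may be in an analysis plan that is not at hand. Its absence from the protocol is therefore not held against it.

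A reader might infer two stronger things. First, that selection on VAS of at least 4 biases the comparison through regression to the mean. It does not: the criterion applies to both randomised arms alike, so regression to the mean cancels in expectation, and the unadjusted comparison is unbiased over randomisation. Only the realised estimate moves with a realised imbalance. Second, that ANCOVA would deal with missing V5 scores. A regression of V5 on V1 loses those patients just as the raw change does.

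**Conclusion.** A cheap improvement, not the correction of an error. The planned primary test is valid; on the protocol's inputs it is not shown to be underpowered, since that depends on which SD the 1.5 is. For a 2-point difference with roughly normal errors, the power gain is about 2 to 18 percentage points if 1.5 is the score SD (ρ from 0.7 down to 0.3, 11 per arm). It is about 4 to 12 points if 1.5 is the change SD (ρ from 0.8 down to 0.3, 12 per arm). The direction is secure under normal errors for moderate ρ; the size rests on a correlation and an SD reading that the documents do not settle. Removal of the effect of chance baseline imbalance on the realised estimate is a further, conditional benefit.

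**What to change.** In Statistical methods used, make the primary analysis an ANCOVA of V5 VAS (average over the last 7 days) on group, with the corresponding V1 average VAS as covariate. Report the adjusted FR-SM difference with its 95% CI. Keep the pre-specified Mann-Whitney test on the change as sensitivity analysis. State in the sample-size section whether 1.5 is the SD of the score or of the change.

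Optionally, replace the four by-visit tests with one repeated-measures model of V2-V5 VAS with baseline, visit, group and group-by-visit. The V5 test among the four repeats the primary comparison.

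The cost is wording, settled before unblinding, with no added patient, visit or measurement. A change to the primary analysis may count as a substantial modification under the protocol's own rules. The statistical price is reliance on near-normal residuals.
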